#### Data Safety and Monitoring Board (DSMB)

The DSMB comprises three senior scientists with expertise in geriatric medicine, exercise, or cognitive training, or RCTs external to the UMN and UR and vetted by the National Institute on Aging (NIA). The DSMB ensures participants’ safety and the integrity and validity of the collected data. One DSMB member will be assigned the role of Chair and Safety Officer. During the project period, DSMB members will have no direct involvement with the study. The chairperson will be responsible for overseeing the meetings and developing the agenda in consultation with the NIA Program Official and the PIs. The DSMB will monitor and review participant safety and data confidentiality, participant accrual and retention, adherence to inclusion and exclusion criteria, adverse events, the quality of data collection, management, and analysis, and study progress; this information will be submitted to the NIA. The DSMB will also monitor the ongoing integrity of the study and review any preliminary data analyses and annual reports submitted by the PIs to the respective Institutional Review Board (IRB) and NIH offices for continuing protection of human participants. The PIs will be informed of serious adverse events as soon as they occur and will notify the IRB, DSMB, and NIA within 5 business days. The DSMB will meet either in person or by teleconference initially following enrollment of 10% of participants and semi-annually after its first meeting.

### Statistical analyses

All variables will be summarized using appropriate descriptive statistics (e.g., means/SD for continuous measures, and frequencies for categorical variables). Baseline variables will be compared among the four groups to determine systematic differences using Pearson’s chi-square test (categorical variables) and analysis of variance (ANOVA) or Kruskal-Wallis (continuous variables), as appropriate. Variables that differ significantly among groups will be included as covariates in the models described below. All analyses will follow the intention-to-treat principle (e.g., group assignment in the analysis will be based on randomized group assignment regardless of level of adherence to provide unbiased comparisons of the effects among the groups). This principle will account for any potential data loss. Because Aims I and II focus on cognition and mechanisms, they will be analyzed regardless of MCI clinical phenotype. We will also compare implementation consistency between sites using Pearson’s chi-square test.

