## Methods

### Design

This RCT will use a single-blind, multi-site, 2 × 2 factorial design, guided by the Consolidated Standards of Reporting Trials (CONSORT) [51] and the Standard Protocol Items: Recommendations for Interventional Trials (SPIRIT) checklist [52]. We will randomize 128 older adults with aMCI equally to one of four arms for 6 months (*n* = 32 in each group): ACT; cycling only; SOP training only; or attention control. Based on our previous studies (Fig. 1) [35, 53, 54], we anticipate screening approximately 384 individuals in person to enroll 128 participants. Participants will then be followed for another 12 months (*n* = 96 at 6 months with 25% attrition and *n* = 84 at 18 months with 35% attrition). We will stratify randomization by site (University of Minnesota [UMN] and University of Rochester [UR]) and age (< 75 and ≥ 75 years), using random permuted blocks of 4 and 8 participants. Cognition and aerobic fitness will be assessed at baseline and at 3, 6, 12, and 18 months; AD signature cortical thickness and DMN at baseline and at 6, 12, and 18 months; AD conversion at 6, 12, and 18 months.

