#### Covariates

Covariates include implementation consistency, global cognition, medical conditions, non-study physical and mental leisure activities (MLAs), premorbid intellect, and adherence. Covariates were selected for their known relationship with cognition and will be measured with psychometrically sound instruments, but they are not all inclusive since randomization will minimize imbalances among groups.

Implementation consistency between sites will be measured using four indicators: participant accruals (number of respondents, enrolled and per group); baseline characteristics (overall and in each group); adherence to the assigned activity and reasons for not adhering; and time to reach key milestones (e.g., initial contact to each screening step, enrollment to baseline, baseline to first activity session, and duration for completing assigned activity). Global cognition will be measured using MoCA. Medical conditions will be assessed using the Medical Changes, Health Service, and Falls Assessment Form, and will include diagnoses, falls, medications, and health service use. Depression will be measured by the Geriatric Depression Scale (GDS). Non-study physical and mental activities will be measured by the MLA questionnaire, a wearable activity monitor, and the Physical Activity Scale for the Elderly (PASE) questionnaire. Daily functioning and mood will be measured using the Activities of Daily Living-Prevention Instrument (ADL-PI, self-administered) and the WHO Disability Assessment Schedule (WHODAS). Premorbid intellect will be assessed using the Wechsler Test of Adult Reading (WTAR).

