#### Aim I. Determine the efficacy and additive/synergistic effects of ACT on cognition over 6 months

We will fit linear mixed-effects models for the change in episodic memory and executive function, accounting for repeated measures at baseline and at the 3 months and 6 months visits (the data for 12 and 18 months will be used in the exploratory aim (Aim III)). Fixed effects in the model will include data collection visit (categorical variable), group assignment, and visit and group interaction. Covariates identified as being imbalanced among groups may be included in the analyses using stepwise variable selection with the Akaike information criterion. A random participant-specific effect will be included to account for correlation between visits in the same participant. The model-based average within-group change in cognition for each group will be computed for each cognitive outcome at both 3 and 6 months. This will allow us to rank the groups in terms of average within-person gains in executive function and episodic memory. We will conduct a composite hypothesis test to assess if the changes at 3 and 6 months differ by groups (similar to a one-factor ANOVA but accounting for repeated measures). In addition, the effect sizes of ACT, SOP training only, and cycling only for cognitive outcomes will also be calculated using standardized mean difference with 95% confidence interval (CI) [(*M*_int_ – *M*_control_ at later time) – (*M*_int_ – *M*
_control_ at baseline)]/intra-participant standard deviation; “int” refers to ACT, SOP training only, or cycling only; “control” here refers to attention control. The effect size of ACT will be compared with the sum of the effect sizes of cycling only and SOP training only to determine the additive/synergistic effect.

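### Covariates are picked by two data-driven rules that disagree, the stated Aim I model omits the randomisation strata, and post-randomisation covariates are not ruled out

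*Protocol article*

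**What the plan says.** All references are to the protocol article.

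- **Statistical analyses, opening paragraph.** "Baseline variables will be compared among the four groups to determine systematic differences", by chi-square, ANOVA or Kruskal-Wallis tests. Then: "Variables that differ significantly among groups will be included as covariates in the models described below". No significance level is given for these tests. The same paragraph commits to analysis by randomised group whatever the level of adherence, so that comparisons are unbiased.
- **Aim I.** "Fixed effects in the model will include data collection visit (categorical variable), group assignment, and visit and group interaction". A participant random effect is added. Then: "Covariates identified as being imbalanced among groups may be included in the analyses using stepwise variable selection with the Akaike information criterion". The Aim II and Aim III subsections build on this model.
- **Design.** "We will stratify randomization by site" and by age group (under 75, 75 and over).
- **Discussion.** The analyses are to incorporate all design features, with site, repeated measures and missing data as examples. Age appears there only as a stratifier of enrolment and an exploratory moderator.
- **Covariates.** "Covariates include implementation consistency, global cognition, medical conditions, non-study physical and mental leisure activities (MLAs), premorbid intellect, and adherence". One of the indicators of implementation consistency is "adherence to the assigned activity and reasons for not adhering". Table 2 shows adherence and non-study activity collected monthly, with no screening or month-0 mark.

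**The concern.** There are three linked problems.

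First, the covariate set is not fixed. In a properly randomised trial a significant baseline difference is a chance event, and its p-value does not show whether the variable predicts the outcome. The stepwise step then uses the outcome data to decide what stays. One rule is mandatory and the other optional, so two analysts following the text could report different primary models.

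Second, site and age group were used to balance the arms, but the only explicit list of model terms contains neither. If they predict change in cognition, leaving them out wastes precision in a trial that expects 96 analysed participants at 6 months.

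Third, adherence to the assigned activity and activity outside the study are observed after randomisation and may depend on arm. Conditioning on them would mean the between-arm contrast no longer rests on randomisation alone, against the stated aim of unbiased comparisons regardless of adherence.

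**Working it through.** The plan gives no figure on this point, so there is none to reproduce. All simulation inputs below are assumptions.

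**1. The two rules side by side.** Rule A (Statistical analyses): significant at baseline, therefore included. Rule B (Aim I): imbalanced, therefore a candidate, kept only if AIC favours it. They give different models whenever AIC drops a significantly imbalanced variable.

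**2. How often chance sets the model.** For k independent tests at level 0.05 (assumed), the probability of at least one significant result is 1 − 0.95^k. Table 2 marks 16 distinct measures at screening or month 0: EXAMINER, RAVLT, BVMT-R, cortical thickness, DMN, cycle test, ISWT, MoCA, ADL-PI, WHODAS, GDS, age, education, gender, race and WTAR.

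- k = 15: 1 − 0.463 = 0.54
- k = 16: 1 − 0.440 = 0.56
- k = 20: 1 − 0.358 = 0.64

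Several of these measures are correlated, which would lower the figures. Conversely, any one covariate, however prognostic, passes a 0.05 screen only 5% of the time, so a useful one is left out 95% of the time.

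**3. Effect on type I error.** Simulation of a four-arm F test on one change score, 24 per arm, ten independent candidate covariates, one of them prognostic. With selection by significance, or by significance then AIC, type I error was 0.047 to 0.051 when the prognostic covariate explained 0% to 30% of the variance, and about 0.035 at 50%. There is no inflation.

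**4. Strata.** If site and age explain a share R² of the variance of *change*, omitting them multiplies the standard error by 1/√(1 − R²):

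- R² = 0.05: 1.03
- R² = 0.10: 1.05
- R² = 0.20: 1.12

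In a change-score simulation (96 participants, four strata), the test without strata became conservative. Type I error was 0.037, 0.020 and 0.010 at R² of 0.10, 0.20 and 0.30, against 0.051 to 0.052 with strata included.

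The Aim I model as written behaves differently. It takes baseline, 3 and 6 months as repeated outcomes and reads the effect from visit by group. Site and age are constant within a person, so their main effects explain mainly between-person variance that the participant random effect already absorbs. Simulating that model (128 participants, within-person correlation 0.5, strata R² of 0.05 and 0.20), the ratio of the month-6 visit-by-group standard error without and with the main effects was 1.000 with complete data, and 1.001 to 1.006 with 25% of month-6 values missing. Adding strata-by-visit terms removed 5% to 13% of excess standard error when strata were assumed to predict change.

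**5. Adherence.** Take a true null contrast, 24 per arm, with adherence and outcome each loading 0.5 on an unmeasured common cause (unit variances). The within-arm slope of outcome on adherence is 0.5 × 0.5 = 0.25. Adjusting then shifts the contrast by 0.25 × the adherence gap:

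- gap 0.5 SD: 0.125 SD (simulated 0.13)
- gap 1.0 SD: 0.25 SD (simulated 0.25)
- no gap: no shift

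The sign follows the direction of the gap and of the shared cause. A gap is plausible: the section on safety, retention and adherence reports 74.3% to 86.4% adherence to cycling and 100% to SOP in earlier studies.

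**The case against.** The strongest reply is that several harsher readings go beyond the text.

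- *Adherence will be adjusted for, so intention-to-treat is broken.* A reader might infer this, but the documents do not say it. The significance screen covers baseline variables, and adherence has no baseline value. No sentence says selection draws on the Covariates list, and grouping by assignment is preserved. Moreover, a participant-level adherence main effect left the visit-by-group estimate unchanged in simulation with complete data, so bias needs a change-score analysis, a time-varying term or a visit interaction. What stands: the article calls adherence a covariate, the Aim I rule refers to imbalanced covariates without limiting them to baseline values, and the way they would enter is not stated.
- *The strata are missing from the analysis.* This is too strong. The Discussion promises to incorporate design features and names site, and its list is by example. What stands: the explicit fixed-effects list has neither factor, and age group is nowhere named as an adjustment term.
- *Omitting the strata inflates standard errors by 3% to 12%.* This does not follow for the stated model. It needs the strata to predict change, which the article does not tell us.
- *Selection inflates false positives.* The simulation in step 3 does not support this.

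It can also be said that covariate lists are commonly left to the analysis plan. That would excuse silence, but here the article states selection rules, and they disagree.

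**Conclusion.** The point holds in a limited form. The article fixes a poor method: baseline significance testing and stepwise AIC, stated as two rules that do not agree. The harm is a model left to chance and some lost precision; the validity of the test is not at risk from selection. The 54% to 64% figure rests on 15 to 20 independent tests at an assumed 0.05.

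The strata point is one of incomplete specification. Its value lies between nothing (site and age do not predict change) and about 5% to 13% of the standard error under assumed effects, and it is realised only through visit interactions. The adherence point is conditional: if a post-randomisation variable were selected and entered so as to affect the change contrast, bias of 0.13 to 0.25 SD in either direction is possible under the assumed gaps and loadings. This is worth correcting before unblinded data are analysed, but it does not undermine the design.

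**What to change.** 1. Delete the baseline significance rule and the stepwise AIC step. Baseline tables can stay descriptive.
2. Prespecify site and age stratum (<75, ≥75), each with its interaction with visit, in the mixed models for Aim I, Hypothesis 2a and Aim III. Main effects alone would barely change the visit-by-group contrast. WTAR may optionally be prespecified in the mixed models as well.
3. Stratify the Aim III log-rank tests by site and age stratum.
4. Handle the baseline outcome once, as the repeated measure already in the model; do not also add it as a covariate.
5. State that only pre-randomisation covariates may enter between-arm comparisons, the mediators of Hypotheses 2b and 2c excepted. Use adherence and non-study activity descriptively or in a labelled secondary analysis.

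The cost is a change of wording and a few degrees of freedom. For Aim I, with three visits, it is 2 main-effect and 2 × 2 interaction coefficients, six in all. No stated sample size changes.

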#### Aim I. Determine the efficacy and additive/synergistic effects of ACT on cognition over 6 months

We will fit linear mixed-effects models for the change in episodic memory and executive function, accounting for repeated measures at baseline and at the 3 months and 6 months visits (the data for 12 and 18 months will be used in the exploratory aim (Aim III)). Fixed effects in the model will include data collection visit (categorical variable), group assignment, and visit and group interaction. Covariates identified as being imbalanced among groups may be included in the analyses using stepwise variable selection with the Akaike information criterion. A random participant-specific effect will be included to account for correlation between visits in the same participant. The model-based average within-group change in cognition for each group will be computed for each cognitive outcome at both 3 and 6 months. This will allow us to rank the groups in terms of average within-person gains in executive function and episodic memory. We will conduct a composite hypothesis test to assess if the changes at 3 and 6 months differ by groups (similar to a one-factor ANOVA but accounting for repeated measures). In addition, the effect sizes of ACT, SOP training only, and cycling only for cognitive outcomes will also be calculated using standardized mean difference with 95% confidence interval (CI) [(*M*_int_ – *M*_control_ at later time) – (*M*_int_ – *M*
_control_ at baseline)]/intra-participant standard deviation; “int” refers to ACT, SOP training only, or cycling only; “control” here refers to attention control. The effect size of ACT will be compared with the sum of the effect sizes of cycling only and SOP training only to determine the additive/synergistic effect.

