#### Sample size and power

We determined the sample size based on anticipated effect sizes, attrition, and the literature. For Aim I, a sample size of 128 at 25% attrition will give us a final analytical sample of 96 at 6 months. Our previous study of SOP training had a partial η^2^ = 0.28 for working memory [35], while cycling had a value *r*^2^ = 0.35 for slowing the worsening of ADAS-Cog (the Alzheimer’s Disease Assessment Scale-Cognition, a global cognition measure [55]. Here, with an estimated, conservative effect size for the change in cognition for ACT (compared with attention control) of 0.25, we will have 80% power to detect group differences in both episodic memory and executive function. For Aim II, our previous study of SOP training had a partial η^2^ = 0.62 for mechanistic effect [35]. Using a type I error rate of 0.05, up to three repeated measures (0, 3, and 6 months), and a correlation between measures of 0.5, we only need 58 participants to have 86% power to detect a significant difference in the change in AD signature cortical thickness and DMN with an effect size (partial η^2^) of 0.08. Aim III is exploratory and not powered. A 35% attrition at 18 months will result in a final analytical sample of 84 to calculate ACT’s long-term effect sizes to inform future RCTs.

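### The Aim I model estimates raw change with free baseline means, losing about 3–25% of the information; if its one participant effect is a random intercept, 6-month intervals and the Aim III test may be too liberal

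*Protocol article*

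**What the plan says.** The Aim I analysis section of the protocol article takes baseline, 3 and 6 months as repeated responses. On the fixed part it says: "Fixed effects in the model will include data collection visit (categorical variable), group assignment, and visit and group interaction". On the random part it says: "A random participant-specific effect will be included to account for correlation between visits in the same participant". No random slope or residual covariance structure is named.

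The effect-size formula in the same section subtracts the whole baseline difference between an active arm and control from the later difference. The baseline score is not a planned adjustment, because covariates enter only after an imbalance is found.

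The Aim I test is a composite test of the 3- and 6-month changes across four arms. Single comparisons with control appear as standardised differences with 95% confidence intervals. Hypothesis 2a uses similar models, and Aim III uses the Aim I model for a composite test at 12 and 18 months.

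The only between-visit correlation given, in Sample size and power, is "a correlation between measures of 0.5", in the Aim II calculation. The Cognition section gives test-retest reliabilities of .78 to .93 for the executive function measure.

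**The concern.** Randomisation makes the true baseline means equal. A model with a free baseline mean in every arm ignores this and subtracts the full chance difference at baseline, which adds noise. With 24 participants per arm at 6 months, precision available from data already collected is worth having.

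A single random intercept with independent residuals also implies the same correlation between any two visits. If correlation falls as visits move apart, the pooled residual variance is too small for the longest change. Standard errors for that change are then too small and its confidence intervals too narrow. The effect on Aim III could be larger, since it uses the model out to 18 months and is meant to supply effect sizes for phase III planning.

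**Working it through.** **Inputs.** Design: "We will randomize 128 older adults with aMCI equally to one of four arms for 6 months", so 32 per arm. Sample size and power: "a sample size of 128 at 25% attrition will give us a final analytical sample of 96 at 6 months", so 96/4 = 24 per arm. Design also gives 84 at 18 months, so 84/4 = 21 per arm. Alpha: "Using a type I error rate of 0.05", stated in the Aim II sentence and taken here as two-sided.

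**The plan's own power figure.** The plan states "conservative effect size for the change in cognition for ACT (compared with attention control) of 0.25" and "we will have 80% power to detect group differences in both episodic memory and executive function". The metric of 0.25 is not named, and the 80% is not reproduced from the inputs stated for Aim I:
- As a standardised mean difference with 24 per arm: 14%.
- As Cohen's f with four arms and 96 analysed: 50% (one-way), 69% (between-group, three visits, correlation 0.5), over 99% (visit by group).
- As η² of 0.25: over 99%.
- Near 80% only with inputs not stated for Aim I, for example 79.5% for the four-arm, three-visit between-group test at correlation 0.3.

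That is a separate matter. The efficiency comparison below is relative and does not depend on it.

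**Efficiency.** Take outcome variance 1 and n per arm.
- Raw change: variance of the difference = (2/n) × 2(1 − ρ).
- Baseline-constrained or baseline-adjusted: (2/n) × (1 − ρ²).
- Ratio = (1 + ρ)/2, so the information lost is (1 − ρ)/2.

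| ρ, baseline to 6 months | Ratio | Lost, complete data | Lost, 25% dropout |
|---|---|---|---|
| 0.5 | 0.75 | 25% | 20% |
| 0.7 | 0.85 | 15% | 12% |
| 0.78 | 0.89 | 11% | 9% |
| 0.93 | 0.965 | 3.5% | 3% |

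The dropout column comes from generalised least squares with equal correlation between visits. Estimating the baseline slope at 24 per arm costs little: simulated ratios are 0.77 at ρ = 0.5 and 0.87 at 0.7. By normal approximation, a contrast with 80% power on raw change would have Φ((1.96 + 0.84)/√ratio − 1.96). That is 90% at ρ = 0.5, 84% at 0.78 and 81% at 0.93.

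**Type I error of single contrasts, if the participant effect is a random intercept with independent residuals.** Assume first-order autoregressive correlation r per 3 months. With visits at 0, 3 and 6 months the pooled residual variance tends to 1 − (2r + r²)/3. The model takes the variance of 6-month change as twice that; the truth is 2(1 − r²). The understatement factor is k = (1 − r²)/(1 − (2r + r²)/3), and the error is 2[1 − Φ(1.96/√k)].
- r = 0.5: k = 0.75/0.583 = 1.286, error 0.084.
- r = 0.7: k = 0.51/0.37 = 1.378, error 0.095.
- r = 0.9: k = 0.19/0.13 = 1.462, error 0.105.

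Simulation at 24 per arm gives 0.084, 0.095 and 0.103. Random slopes of moderate to strong size give 0.067 to 0.135. For the single 3-month contrast the numerator of k becomes 1 − r, and the error is below nominal: 0.034, 0.030 and 0.025.

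**Composite tests, same assumptions, simulated on complete data.**

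| r per 3 months | Aim I composite (3 and 6 months, 24 per arm) | Aim III composite (12 and 18 months, 21 per arm) |
|---|---|---|
| 0.5 | 0.055 | 0.082 |
| 0.7 | 0.059 | 0.109 |
| 0.9 | 0.063 | 0.147 |

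Under a random walk the Aim I composite test is at 0.065, and under random slopes at 0.052 to 0.078. With 25% dropout and r = 0.7, the single 6-month contrast is at 0.085 and the Aim I composite at 0.055 (600 runs, so a standard error of about 0.01). When correlation really is equal between all visits, every test is close to 0.05.

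**The case against.** Difference in raw change from visit, group and visit-by-group terms is a conventional analysis and is unbiased under randomisation. Three stronger readings are tempting, and the document does not support them.

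- **That a quarter of the information is lost, so that 96 analysed participants could carry the information of 128 (96/0.75).** This needs complete data and a correlation of 0.5, which the protocol states only for Aim II. The reliabilities for executive function point to 11% down to 3.5%, although reliability is only an upper guide to a 6-month correlation.
- **That the Aim I test has double its nominal error.** The composite test averages over a 3-month change that is tested conservatively and a 6-month change that is tested liberally, and it ends only slightly above 5%. The near-doubling belongs to the single 6-month contrast. The protocol reports that contrast only as an effect size with a 95% interval, and does not say how the interval is computed.
- **That the covariance is wrongly specified.** The text says a participant-specific effect. It does not say intercept only, and it does not say independent residuals. That is the natural reading, but a statistical analysis plan that is not shown may fix the structure differently.

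The autoregressive scenarios are also assumptions, some of them severe: 0.7 per 3 months implies 0.7⁶ = 0.12 at 18 months. The worst cases do not coincide either. At 0.9 per 3 months the 6-month correlation is 0.81 and the efficiency loss is only (1 − 0.81)/2 = 9.5%. Aim III is exploratory and not powered.

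All of this stands as a limit on size. It does not remove the efficiency point, which follows from fixed effects and an effect-size formula that the protocol does state.

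**Conclusion.** The point holds in a limited form. The stated model gives an unbiased estimate that is less efficient than the available alternative by about 3–25% for correlations from 0.93 down to 0.5. The alternative is never worse, apart from a small cost of estimating the baseline slope.

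The error-rate part is conditional on a random intercept with independent residuals and on correlation that decays with time. Under those assumptions, single 6-month contrasts, and 95% intervals taken from this model, have about 8–10% error. The Aim III composite test has about 8–15%, and the Aim I composite test about 5.5–6.5%. Decay over 18 months is plausible in a population where the protocol expects both conversion and reversion, but the document gives no figure for it. A reader should not conclude that the Aim I estimate is biased or that its main test is invalid.

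**What to change.** In the Aim I analysis section, carried through to Aims II and III:
- Fit the model with one baseline mean common to all arms. Alternatively, use the baseline outcome as a covariate with a baseline-by-visit term, so that the responses are the post-baseline visits.
- Use an unstructured within-participant covariance with small-sample degrees of freedom, and name a fallback structure in case of non-convergence.
- Derive the effect-size intervals from this model.

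The change is to analysis wording and needs no new data. The downside is a few more covariance parameters: 3 × 4/2 = 6 for three visits and 5 × 6/2 = 15 for five. The fallback matters most for Aim III, where about 84 participants remain. If an analysis plan already specifies the covariance, only the baseline change is needed.
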